## Main adverse events and reactions expected in this trial

According to clinical trials and post-marketing use-results surveys of ARGI-U ^®^ combination granules, nausea, nausea, vomiting, diarrhoea, scratchiness and abnormal liver function were reported as the main adverse reactions.

Care should be taken throughout this clinical trial.

### Major adverse events foreseen in this trial

1. Nausea, nausea and vomiting
2. Diarrhoea
3. Feeling that one's skin is itchy
4. Abnormal liver function (increased AST, ALT, ALP)

The frequency of occurrence, calculated from the combined results of clinical trials and post-marketing surveillance up to the time of approval, ranged from 0.1% to less than 5% in all cases.

## Response to adverse events.

### Dealing with anticipated adverse events.

In the event of an adverse event, the investigators and sub-investigators should provide appropriate first aid, pay attention to ensuring the safety of the subject, and endeavour to resolve and investigate the cause by having the subject undergo diagnosis and treatment by a specialist physician when necessary.

For each anticipated adverse event, take the following actions

1. For nausea, nausea and vomiting, careful follow-up or antiemetics should be administered according to symptoms.
2. For diarrhoea, careful follow-up or intestinal regulators should be administered according to symptoms.
3. Careful follow-up or anti-allergic agents should be administered for itching, depending on the symptoms.
4. If liver function abnormalities (increased AST, ALT, ALP) exceed three times the upper limit of the institutional reference value, the investigator (subcontractor) will inform the study coordinating investigator of the results of a thorough examination of the causal relationship with the investigational drug and discuss the need to discontinue the investigational drug.

### Follow-up of adverse events that cannot be ruled out as causally related to the investigational drug

Adverse events occurring during the trial period should be followed up as far as possible until recovery occurs or the event is deemed no longer clinically necessary. The method of inpatient or outpatient visits, or in the case of outpatients, the frequency of visits and test items, etc., should be determined by the investigator or sub-investigator, depending on the type and severity of the relevant adverse event. However, if there is a reasonable reason to terminate the investigation in the middle of the study, the investigator or sub-investigator may terminate the follow-up investigation by stating the reason in the original documents such as the medical record.

### Records of adverse events when they occur.

The investigator or sub-investigator should describe in the case report the name of the adverse event, date of onset, severity, severity (non-serious and serious), causal relationship to the investigational drug, treatment, outcome and date of outcome.

## Handling of serious adverse events.

If an adverse event occurs in a subject receiving an investigational drug and the investigator or others consider the event to be serious as per section 11.2.5, the adverse event information should be handled according to the following procedure.

Details on how to respond to the occurrence of a serious adverse event are in accordance with the Procedures for Handling Safety Information.

1) Reporting from the investigator to the head of the site, the clinical trial coordinator and the investigational drug provider

The investigator should report such adverse event information as soon as possible to the head of the investigational medical institution, regardless of causal relationship, as well as to the trial co-ordinator and the investigational drug provider.

2) Notification by the clinical trial coordinator to the investigators at each site

The clinical trial co-ordinator reviews the content of the adverse event report obtained from the investigator and notifies the relevant adverse event information to the investigators at each of the other sites.

3) Discussions between the investigator and the coordinating investigator

The investigator at each site checks the report obtained from the clinical trial co-ordinator, discusses it with the clinical trial co-ordinator as necessary and reports his/her opinion as the clinical trial co-ordinator (including the need for a report to the Minister of Health, Labour and Welfare) to the clinical trial co-ordinator.

4) Report to the Minister of Health, Labour and Welfare

If a report to the Minister of Health, Labour and Welfare is required, the Clinical Trial Co-ordinator should prepare Forms 7 and 8 and an organising sheet and report to the National Institute for Pharmaceuticals and Medical Devices (hereinafter referred to as 'NHI').

5) Reporting to the head of the implementing medical institution

When a report is made to the Minister of Health, Labour and Welfare on a serious adverse event that occurred at another medical institution, the investigator should report the contents of Forms 7 and 8, obtained from the clinical trial coordinator, to the head of the implementing medical institution as soon as possible.

6) Action to be taken when additional information is available.

The investigator at the site where the adverse event occurred should make an additional report to the head of the site as soon as possible when additional information on the event is obtained, as well as to the trial co-ordinator and the trial drug provider. The handling of such additional information should be in accordance with the procedures described in (1) to (5) of this section, and reports should be made to the Agency as necessary.

## Handling of safety information obtained during clinical trials.

The clinical trial coordinator will endeavour to collect information and other information (foreign case information, action reports and research reports) concerning the study's investigational drug. Details on how to respond when safety information is obtained will be in accordance with the 'Procedures for handling safety information'.

If the investigator obtains information on the quality and safety of the active drug or other information important for the proper conduct of the clinical trial, he/she prepares a 'Report on Safety Information' and reports it to the head of the implementing medical institution.

The investigator or sub-investigator should immediately explain orally to the currently participating subject any new findings that affect the subject's intention. After submitting the revised consent document to the Clinical Trial Review Committee and obtaining its approval, a new explanation document should be used to explain the new findings to the currently participating subjects and consent for continued participation should be obtained in writing again, except for subjects for whom the observation period has already ended. New findings that affect the subject's intention refer, for example, to information on new adverse events related to the treatment or information on the development of new treatments for the disease in question.

## Pregnancy and maternity and when obtaining information on childbirth

If a patient is found to be pregnant during the course of the study, the administration of the investigational drug should be discontinued immediately and recorded in the adverse event section of the source documents. The investigator or sub-investigator should follow up to the birth and report the health status of the mother and child to the head of the implementing medical institution. The reporting procedure should be in accordance with the 'Procedures for handling safety information'.

If a patient's partner is found to be pregnant, the trial will not be stopped. Pregnancy of the patient's partner is not considered an adverse event. However, if possible, the investigator or sub-investigator should follow up and record the birth.

# Effectiveness and Safety Assessment Committee

The committee consists of members with the expertise required for the evaluation of the trial and provides appropriate advice and recommendations to the trial coordinator from a neutral standpoint to ensure patient safety and the ethical and scientific validity of the conduct of the trial. The procedures of the Effectiveness and Safety Assessment Committee should follow the 'Procedures for the Effectiveness and Safety Assessment Committee' to be prepared separately.

# Ethical and scientific conduct of clinical trials

## Compliance with laws and regulations

This clinical trial should be conducted in accordance with the ethical principles of the Declaration of Helsinki, and in compliance with the Act on Quality, Efficacy and Safety Assurance of Pharmaceuticals and Medical Devices, its Enforcement Order, its Enforcement Regulations, the GCP Ministerial Ordinance, notices related to the GCP Ministerial Ordinance (hereinafter collectively referred to as 'GCP Ministerial Ordinance etc.') and this Clinical Trial Implementation Plan. The following conditions should be complied with.

## Clinical Trial Review Committee

Prior to the conduct of the trial, the Clinical Trial Review Committee deliberates on the conduct of the trial from the perspective of ethical, scientific and medical relevance. In addition, the Clinical Trial Review Committee will review any changes to the trial. If the study lasts longer than one year, the Trial Review Committee will continuously review whether the study is being conducted properly at least once a year.

## Preservation of confidentiality of test subjects

The investigators and sub-investigators should take the human rights of the subjects into consideration and endeavour to protect their personal information. Subjects should be identified by subject identification codes in the subject enrolment and case report forms, and those involved in this clinical trial should maintain the confidentiality of subjects in the direct inspection of original documents, publication in medical journals and submission of documents to regulatory authorities, etc. related to the conduct of the clinical trial.

# Statistical matters

## Definition of the analysis population

### Safety analysis population

The population of enrolled cases, excluding the following subjects, is the population for the safety analysis.

Cases not treated with investigational drug

Subjects with no safety observations at all after administration of the investigational drug

### Efficacy analysis population

The population of enrolled cases excluding the following subjects is the population subject to efficacy analysis (FAS: Full analysis set).

Cases not treated with investigational drug

Subjects with no measurements at all on the assessment of efficacy

For the primary endpoint, an analysis using a subject population (PPS: Per Protocol Set) compliant with the study protocol will also be conducted to assess the stability of the FAS analysis results.

## Criteria for handling cases

Cases should be handled as follows.

1) Ineligible cases.

Cases in breach of the 'inclusion criteria', cases in breach of the 'exclusion criteria' and cases of GCP non-compliance are ineligible cases.

2) Cases of discontinuation or drop-out prior to administration of the investigational drug

Cases of discontinuation or drop-out prior to investigational drug administration (see 3) below) are not included in the analysis population.

3) Cases of discontinuation or drop-out after administration of an investigational drug

Cases that withdrew consent, did not fulfil the 'inclusion criteria', were in conflict with the 'exclusion criteria', or were discontinued according to the criteria for discontinuation of the trial for each subject as indicated in 'Criteria for discontinuation of the trial for each subject' should be considered as discontinued cases. In addition, cases that are untraceable due to reasons not directly related to the trial should be considered as drop-out cases. These cases will be included in the analysis with the amount of change in the score at the last visit from before medication.

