| **Drugs prohibited for use in combination with other drugs** | All concomitant medications (including Seresist^🄬^ (tartirelin hydrate) and Hyltonin Injection^🄬^ (protirelin tartrate hydrate)) are permitted during the study period. However, the dose should be constant for 4 weeks prior to the start of investigational drug administration. Celist^🄬^ (Tartirelin hydrate), Hyltonin Injection^🄬^ (Protilerin tartrate hydrate) and phosphodiesterase 5 inhibitors are not permitted to be started or discontinued during a clinical trial and any cases of initiation or discontinuation will be treated as drop-out or discontinuation cases. |
| **Safety assessment.** | Vital signs (temperature, blood pressure, pulse), body weight, adverse events, haematology, blood biochemistry and urinalysis are performed before enrolment, on the first day of treatment and after 4, 8, 16, 24, 32, 40, 48 and 52 weeks of treatment to assess safety. |
| **Efficacy primary endpoint** | SARA 'total' score after 48 weeks  (The primary endpoint is the change from baseline in the SARA 'total' score at the final assessment of the treatment period.) |
| **Efficacy secondary endpoints** | 1. SARA 'total' scores after 4, 8, 16, 24, 32, 40 and 48 weeks 2. SARA 'Walking, standing' score. 3. SARA Scores for each item (except walking and standing scores) 4. Gravity body sway test (total trajectory length for 30 s, rectangular area) 5. Timed Up and Go Test (TUG) (minimum time) 6. Beck Depression Inventory-II (BDI-II) 7. Clinical Global Impression (CGI) 8. Patient Global Impression of Improvement (PGI-I) 9. Short-Form 8 (SF-8) |

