### Rationale for setting the duration of administration

Traditionally, treatment intervention trials in spinocerebellar degeneration have used the SARA (the Scale for the Assessment and Rating of Ataxia) total score as the primary endpoint, often for a treatment period of 8 to 48 weeks (12 months) (2-5,31-34) . SARA annual changes in natural history have been reported to range from 1.3 to 1.6 for SCA6 and 1.1 to 1.6 for MJD/SCA3 (35-38) . The current investigational drug suppresses polyglutamatergic pathology and does not achieve a dramatic improvement in symptoms; when SARA is the primary endpoint, a somewhat longer observation period is required to determine the effect of treatment on the suppression of progression of slight progression of symptoms as a therapeutic effect. Therefore, based on the results of clinical trials conducted to date with other drugs in spinocerebellar degeneration, the duration of treatment in the clinical trials was set at 12 months.

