### Efficacy primary endpoint

Change from baseline in SARA 'total' score at 48 weeks post-treatment.

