## Prohibited drugs and drug-free treatment

All concomitant medications (including Seresist^🄬^ (tartirelin hydrate) and Hyltonin Injection^🄬^ (protirelin tartrate hydrate)) are permitted during the study period. However, the dose should be kept as constant as possible for 4 weeks prior to the start of investigational drug administration. For Seresist^🄬^ (tartirelin hydrate), Hyltonin Injection^🄬^ (protilerin tartrate hydrate) and phosphodiesterase 5 inhibitors, initiation or discontinuation during a clinical trial is not permitted and any initiation or discontinuation is treated as a drop-out or discontinuation case. The investigator (sub-investigator) or collaborator should be instructed to promptly inform the investigator (sub-investigator) or collaborator of any changes in concomitant medication.

Rehabilitation started at the time of enrolment in the clinical trial will continue without any change in content. No new rehabilitation will be initiated throughout the duration of the clinical trial.

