### Analysis of efficacy endpoints

1) Primary endpoint (SARA total score after 48 weeks of treatment)

The change in SARA total score from baseline to 48 weeks post-dose is compared for the test vs control group by analysis of covariance, with baseline as the covariate and the investigational drug group (active drug group and placebo group) as the fixed effect.

2) Secondary endpoints.

SARA total score change through 48 weeks.

SARA total scores are summed for each assessment period, and the total is then subjected to a general linear mixed-effects model with the change in time (4, 8, 16, 24, 32, 36, 40 and 48 weeks) as the response variable, the investigational drug group (active drug group vs placebo group), time and baseline as fixed effects and subjects as variable effects Examine the interaction between time and investigational drug group. Multiplicity is not considered.

SARA 'walking, standing' score.

As per the method of analysis of the SARA 'total' score through 48 weeks.

SARA Scores for each item

Same analysis method for SARA 'total' scores through 48 weeks, except for the combined 'walking' and 'standing' scores for each SARA item.

Gravity body sway test

A summary of the change in total trajectory length and rectangular area (‘values after 48 weeks’ treatment’ – ‘baseline values’) obtained during the 30-second gravity body sway test is shown for each group at the time of the final assessment. Cases with a negative change are defined as improved cases, and the distribution of improved cases at the time of the final assessment is shown for each group.

TUGT.

A summary at the time of the final assessment is given for each group for the shortest time change between the two tests ('value after 48 weeks' treatment' - 'baseline value'). Cases with a negative change are defined as improved cases, and the distribution of improved cases at the time of the final assessment is shown for each group.

BDI-II.

A summary of the change in the two tests ('value after 48 weeks' treatment' - 'baseline value') at the time of the final assessment is presented for each group. Cases with a negative change are defined as improved cases, and the distribution of improved cases at the time of the final assessment is shown for each group.

CGI-S.

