A summary of the amount of change in tests at each time point ('value at each time point' - 'baseline value') is presented for each group at each assessment time point. Cases with a negative amount of change are defined as improved cases, and the distribution of improved cases at each assessment time point for each group is shown.

CGI, PGI-I.

A summary at each assessment time point is given for each group.

SF-8.

A summary of the change in the two tests ('value after 48 weeks' treatment' - 'baseline value') at the time of the final assessment is presented for each group. Cases with a negative change are defined as improved cases, and the distribution of improved cases at the time of the final assessment is shown for each group.

3) Descriptive statistics, diagrams and tables

For each endpoint, calculate frequencies, proportions and 95% confidence intervals for the counts, and descriptive statistics (number of cases evaluated, mean, SD, minimum, median, maximum and 95% confidence interval) for the quantitative values, by study group and time of evaluation, as appropriate. Where necessary, drawings and tables are made.

4) Significance level

Two-sided α = 0.15 for subject background bias, one-sided α = 0.025 for the others.

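### Last-visit substitution for dropouts biases the primary SARA comparison towards the arm that loses patients earlier, and dilutes a true slowing when dropout is equal

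*Protocol*

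**What the plan says.** Section 8.4.2 of the protocol defines the primary endpoint as "Change from baseline in SARA 'total' score at 48 weeks post-treatment". The summary gives Week 48 too, then adds in brackets: "The primary endpoint is the change from baseline in the SARA 'total' score at the final assessment of the treatment period". Section 14.3.3 sets the analysis: "The change in SARA total score from baseline to 48 weeks post-dose is compared for the test vs control group by analysis of covariance". Treatment group is the fixed effect, and the model adjusts for the baseline score. The test level is "one-sided α = 0.025 for the others".

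Section 14.2, item 3, sets the rule for patients who stop or are lost after dosing: "These cases will be included in the analysis with the amount of change in the score at the last visit from before medication". Two other provisions feed this rule:
- Section 10.2 ends a subject's trial when adverse events make dosing hard to continue.
- Section 9.2 covers starting or stopping certain drugs: "any initiation or discontinuation is treated as a drop-out or discontinuation case".

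Section 8.5.2 asks for SARA at discontinuation only where feasible, and its absence is not a deviation. After discontinuation, section 10.3 specifies only a safety check.

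Section 8.3.4 gives the expected course: "SARA annual changes in natural history have been reported to range from 1.3 to 1.6 for SCA6". It also says that the drug "does not achieve a dramatic improvement in symptoms". The treatment period is long because a slight slowing needs time to show.

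**The concern.** The endpoint measures accumulated worsening, so its expected size depends on how long a patient is observed. A short observation carried to Week 48 looks like slow progression, which is the effect that the trial hopes to find. The long treatment period was chosen to let a small difference emerge, and the substitution rule gives that up for every patient who leaves.

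If the arms lose patients in different numbers or at different times, the primary comparison shifts towards the arm with earlier losses. If losses are equal, there is no false benefit, but a true slowing is diluted. Section 8.4.3 regards even a slight SARA advantage over placebo as clinically meaningful, so a shift of one or two tenths of a point could matter to the interpretation.

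The planned safeguards do not remove the problem. The per-protocol analysis in section 14.1.2 is a selected subset. The all-visit mixed model in section 14.3.3 is only secondary.

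**Working it through.** The protocol sets its sample size by feasibility and gives no power calculation, effect size, SD or dropout rate. There is no figure to reproduce.

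**Inputs from the protocol**
- Progression m = 1.3 to 1.6 points a year (8.3.4).
- On-treatment SARA visits at Weeks 4, 8, 16, 24, 32, 40 and 48 (8.5.1).
- 20 patients per arm (8.2); one-sided level 0.025 (14.3.3).

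**Assumptions**
- Linear worsening.
- Dropout proportions and timing as stated in each scenario.
- Slope SD 0.75 to 1.5 points a year and visit noise SD 0.5 to 1.0. The SD of the 48-week change is then between √((0.75 × 48/52)² + 2 × 0.5²) = 0.99 and √((1.5 × 48/52)² + 2 × 1.0²) = 1.98.

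**Step 1: score given to one dropout.** Expected change at Week 48 is m × 48/52 = 1.20 to 1.48. The carried value is m × t/52.

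| Last visit | Scored change | Shortfall against Week 48 |
|---|---|---|
| Week 4 | 0.10 to 0.12 | 1.10 to 1.35 |
| Week 8 | 0.20 to 0.25 | 1.00 to 1.23 |
| Week 24 | 0.60 to 0.74 | 0.60 to 0.74 |

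**Step 2: false benefit with an inert drug.** B = (p_active − p_placebo) × m × (48 − t̄)/52, where t̄ is the mean week of the last visit.
- Last visits at Weeks 4, 8 or 16: t̄ = 28/3 = 9.33. At 20% against 5%, B = 0.15 × 1.3 × 38.67/52 = 0.145, and 0.178 with m = 1.6.
- Last visits spread over Weeks 4 to 40: t̄ = 124/6 = 20.67. At 20% against 5%, B = 0.15 × 1.3 × 27.33/52 = 0.10, and 0.13 with m = 1.6.
- Upper scenario, 30% against 5% at Weeks 4 to 16: B = 0.25 × 1.3 × 38.67/52 = 0.24, and 0.30 with m = 1.6.
- Mild scenario, 12.5% against 5%, spread: B = 0.075 × 1.3 × 27.33/52 = 0.05, and 0.06 with m = 1.6.

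If placebo loses more patients, the sign reverses.

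**Step 3: one-sided error.** As an approximation, error = 1 − Φ(1.96 − B/(SD × √(2/20))). With B = 0.15 and SD = 1.5, 0.15/(1.5 × 0.316) = 0.316, and 1 − Φ(1.644) = 5.0%. With SD = 3 it is 3.6%. Simulation of the planned ANCOVA over the assumed SDs gave:
- No dropout: 2.3 to 2.7%.
- 20% against 5%: 4.2 to 7.6% with early dropout, 3.9 to 5.7% when spread.
- 12.5% against 5%, spread: 3.0 to 3.7%.
- 5% active against 20% placebo at Week 8 (slope SD and visit noise SD both 1.0): 0.8%, with a bias of 0.17 points against the drug.

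**Step 4: equal dropout with a true effect.** The fraction lost is p × (48 − t̄)/48 = 0.20 × 38.67/48 = 16%. A 50% slowing at m = 1.45 is 0.5 × 1.45 × 48/52 = 0.67 points, and it falls to 0.67 × 0.84 = 0.56. Simulated power falls from about 23% to 17 or 18% (slope SD and visit noise SD both 1.0).

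**Step 5: the remedy.** In simulation, a Week 48 contrast from a repeated-measures model on all observed visits removed the bias. Its standard error was about 3 to 7% larger. The model was fitted with the true covariance, so estimating an unstructured matrix from 40 patients was not tested.

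**The case against.** The strongest reply is that the documents do not show a dropout imbalance. Section 3.2.5 reports adverse reactions of any kind, not discontinuations, in 12.5% of 40 trial patients and 8.1% of 222 patients after marketing. Section 11.3.1 puts each expected reaction below 5%. The frequent diarrhoea in section 8.3.3 followed a dose above the trial dose. Those were other populations, so higher dropout is possible, but a reader should not infer that the protocol predicts heavy loss on active drug. The 30% against 5% case, and the error of about 14% reached only with the smallest assumed SDs and the steepest progression, are upper scenarios.

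The direction is also open. Placebo patients who worsen, start a restricted drug and are counted as dropouts would bias the result against the drug. Fast progressors leaving the active arm would offset part of a false benefit. Linear worsening is an assumption, because section 8.3.4 gives annual change only.

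Two stronger readings are tempting and fail:
- **That carried values make the standard error wrong.** In simulation the model standard error agreed with the empirical spread within about 3%, and with equal dropout the error stayed near 2.5%. The fault is a shift in the mean.
- **That there are two rival primary endpoints.** The summary, 8.4.2, 14.2 and 14.3.3 can be read as one endpoint at Week 48 plus one substitution rule, with the bracketed summary wording expressing that rule. The wording is loose, but it does not establish two primary results.

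Finally, the trial is a small exploratory study, an all-visit mixed model is already planned, and a separate analysis plan may add sensitivity analyses. This lowers the severity. It does not cure the rule, which the protocol itself fixes for the analysis.

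**Conclusion.** The point holds as a bias in the mean of the primary comparison. It arises whenever dropout differs between arms in amount or timing, and it favours the arm that loses patients earlier. For 20% against 5% dropout and an inert drug, it is about 0.10 to 0.18 points, or 0.15 × 27.33/48 = 9% to 0.15 × 38.67/48 = 12% of the expected 48-week worsening. The one-sided error is then roughly 4 to 7.5%, and lower if the true SD is larger than assumed. With 20% early dropout in both arms, a true slowing shrinks by about 16%.

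The mechanism rests on the protocol's own progression rate and substitution rule. The sizes rest on assumed dropout, timing, SDs and linear worsening. The documents do not support a claim that a false benefit for the active arm is to be expected. Severity: should be fixed, since it affects the only primary test and is cheap to correct.

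**What to change.** 1. State the primary endpoint in the summary, 8.4.2 and 14.3.3 in one form: change from baseline in SARA total score to Week 48.
2. Remove last-visit substitution from section 14.2 as the primary rule.
3. Make the primary analysis the Week 48 treatment contrast from a repeated-measures model on all observed on-treatment SARA visits, with arm, visit, arm by visit and baseline. Use unstructured covariance and Kenward-Roger degrees of freedom. Seven visits need 7 × 8/2 = 28 covariance parameters from 40 patients, so name the fallback in advance, for example heterogeneous Toeplitz, then AR(1).
4. Align the visit list in section 14.3.3 with the schedule. It includes Week 36, which has no SARA visit in section 8.5.1.
5. Keep the ANCOVA with last-visit values as a sensitivity analysis.

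Continued SARA visits after study drug is stopped are optional. If they are added, the protocol must first say whether the target is the effect regardless of stopping or the effect while on treatment, because off-treatment data answer only the former directly.

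The cost is protocol and analysis-plan wording, a slightly wider interval (standard error about 3 to 7% larger in simulation), and reliance on a missing-at-random assumption. No extra patients are needed.
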